- Operational integration of Early Infant Diagnosis (EID) and Expanded Program of Immunization (EPI)
- Training and orientation of health facility staff to deliver intervention messages to mothers of children under five years

1. Control: Usual standard of care.

We will then evaluate the two interventions in comparison to the control group, as well compare the two intervention groups to each other, in terms of specific outcomes (See the power calculations section for specific outcome variables) by a review of clinic records collected over the period of the study.

We will supplement and triangulate the data obtained from the clinic records through four primary data collection tools:

- Focus Group #1: Mothers who have recently attended Under-5 clinics
- Focus Group #2: Health facility workers in sampled health facilities Interview guide for exit interviews for mothers done at health facilities
- Interview guide for data verification for mothers done in local communities

Random sampling will be done at the health facility level to separate health facilities in the sample frame into 4 groups – 1) Comparison 2) Simple Intervention 3) Comprehensive Intervention and 4) Not in the study sample. Sampling will be conducted using STATA IC Version 12 with a pre-set seeds to allow for post-randomization verification of selection methods. There are 77 clinics in the sample frame spread across three districts in Southern Province in Zambia. The sample will be stratified by urban/rural divide and by district. Please see the table below for information on the stratification within the sample frame and sample respectively.

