It has been determined that a sample of 60 facilities (20 facilities for each evaluation group) – selected out of the sample frame of 77 facilities – is required for the study.  The sample will be stratified by an urban/rural divide and district, with a third of the sites randomly chosen as comparison facilities, a third randomly chosen as Simple Intervention facilities, and the final third randomly chosen as Comprehensive Intervention facilities. Thus, the unit of randomization will be the health facility and all infants attending the given health facility for immunizations during the period of the evaluation will be the cluster.  Random assignment and post randomization checks will ensure that on average, observable and unobservable characteristics of the program and comparison groups are statistically similar. Observable characteristics that will be checked for balance across evaluation arms include baseline HIV testing rates, baseline immunization rates, number of ART sites, and catchment population sizes. In doing so, any difference in outcomes between program and comparison group can be causally attributed to the intervention. In total, we will have 60 clinics in the study, each of which see on average around 260 infants for their first immunization each year. To calculate the number of infants we expect to see, in our study, we divide 260 in half (we will only collect data for 6 months) and then we will take 75% of this remaining number (to account for around 25% of immunizations which will be done on outreach). This yields around 98 babies per facility multiplied by 60 facilities for a total of 5,880 infants. If we count mothers and infants as separate entities, we get a total of 11,760 participants. Up to 5% of the mothers/care givers in the study sample will be selected for data verification and a separate 5% of mothers will be selected for exit interviews, which is 294 mothers for each group. Additionally, up to 30 focus groups will be held, 15 for recent mothers and 15 with facility staff, with each focus group including no more than 10 individuals. The 150 mothers participating in the focus group are already included in the 11,760 participants. The 150 health facility staff participating in the focus groups are all new participants and must be added to the 11,760 participant number for a total of 11,910.

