This study is designed to measure the impact of the Simple Intervention and Comprehensive Intervention on the number of women and infants tested and identified as HIV-positive as well as the percentage uptake of certain immunizations. Statistical power calculations are based on the immunization uptake outcome variable, as this is the indicator with the smallest effect size required to be policy-relevant. The study will test the following null hypotheses:

- - 1. Infants are not less likely to attend immunization clinics for DPT1, OPV1, DPT2 and OPV2 immunizations in Comprehensive Intervention health facilities versus the combination of the Simple Intervention and Comparison health facilities
    2. Rapid HIV antibody tests are not more likely to be administered in:
       1. Simple Intervention facilities versus Comparison facilities
       2. Comprehensive Intervention facilities versus Simple Intervention facilities
    3. DNA PCR tests are not more likely to be administered in:
       1. Simple Intervention facilities versus Comparison facilities
       2. Comprehensive Intervention facilities versus Simple Intervention facilities
    4. Mothers are not more likely to be identified as HIV-positive in:
       1. Simple Intervention facilities versus Comparison facilities
       2. Comprehensive Intervention facilities versus Simple Intervention facilities

Below are the power calculation for each of the outcomes we intend to measure:

*Effect of Comprehensive Intervention on immunization rates*

- **Level of outcome:** DPT 1 immunization
- **Sample:**
  - 20 Comprehensive Intervention facilities compared to 40 Simple Intervention and Comparison facilities
  - 98 new infants per facility
- **Detectable percentage point decrease in immunization uptake:** 10%
- **95% plausibility interval:** Expected probability that an infant receives DPT1 immunization is 87% with bounds around this estimate from 55 – 95%
- **Significance level:** 5%
- **Power:** 86%^[[29]](#footnote-7)^

*Effect of Simple Intervention on rapid HIV antibody testing rates (Simple versus Comparison facilities)*

- **Level of outcome:** Rapid HIV antibody tests administered
- **Sample:**
  - 20 Simple Intervention facilities compared to 20 Comparison facilities
  - 98 new infants per facility
- **Detectable percentage point increase in antibody tests:** 5%

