- **95% plausibility interval:** Expected probability that a mother is identified as HIV-positive is 0.2% with bounds around this estimate from 0.1 – 1.0%
- **Significance level:** 5%
- **Power:** 76%

*Effect of Comprehensive Intervention on percentage of new mothers identified as HIV-positive (Comprehensive versus Simple facilities)*

- **Level of outcome:** HIV-positive mothers identified
- **Sample:**
  - 20 Comprehensive Intervention facilities compared to 20 Simple Intervention facilities
  - 98 mother/infant pairs per facility
- **Detectable percentage point increase in HIV-positive mothers identified:** 1.5%
- **95% plausibility interval:** Expected probability that a mother is identified as HIV-positive is 1.0% with bounds around this estimate from 0.5% – 2.0%
- **Significance level:** 5%
- **Power:** 87%

These power calculations represent lower bounds, as covariate analysis will further increase the actual power of the evaluation. We can assume that because all research questions are sufficiently powered to detect effects between either the comprehensive and simple facilities or the simple facilities and the comparison facilities, all research questions are sufficiently powered to evaluate effects between the comprehensive and comparison clinics in the case where the simple clinics show no effect.

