There is a low risk of John Henry effect, the process in an evaluation by which the comparison group realizes that it is a comparison group and changes its behavior in response. Patients are unlikely to realize they are in comparison catchment areas and change their behavior in any way other than outlined in the spillover section. There exists a risk that comparison facilities could take steps to improve EID services that they would not have done in the absence of the evaluation. The research team will attempt to measure this by comparing EID testing rates from before the intervention with testing rates during the evaluation.

There is a low risk of any survey effects for this evaluation. No surveys with durations of over 30 minutes at a time are expected. Because the main outcomes are directly observed, not asked of the respondents, any survey effects are likely to be minimal.

*Site Attrition*

All sites included in the randomization will have appropriate infrastructure and staffing levels to participate in the study. Thus, it is unlikely that facilities will drop out from the study due to inability to implement the intervention. Because unexpected changes to staffing levels may still lead to attrition, additional facilities have been included in the sample size calculations to ensure adequate statistical power in the event of such occurrence.

*Patient attrition*

Patient-level attrition could manifest itself due to incorrect facility register recordings. This will be minimized through training and regular monitoring of facility health staff on proper register data collection. Respondent attrition is possible for those who do not consent to exit interviews. However, these activities are not central to the core analysis.

Bounds analysis will be used to account for any attrition in the ultimate analysis.

*Impact heterogeneity*

Facility registers provide important baseline data on HIV testing, EID, and EPI services and other patient characteristics. Additional baseline information on facility staff, equipment and buildings will be collected. This information will allow the study team to calculate whether the intervention had a differential impact across important variables.

Ethical Issues

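### The protocol says spare facilities protect power against site attrition, but its power figures use every facility in the arms compared, and two Simple versus Comparison contrasts are below 80% before any loss

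*Protocol*

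**What the plan says.** Three parts of the protocol bear on this.

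- **Technical study risks and potential biases, Site Attrition.** Drop-out through inability to implement is called unlikely, but staffing changes may still cause loss. The stated safeguard is that "additional facilities have been included in the sample size calculations to ensure adequate statistical power in the event of such occurrence". No number or rate is given.
- **Sample Size and Justification.** Sixty facilities, 20 per arm, are "selected out of the sample frame of 77 facilities – is required for the study". The participant count applies the same 60 with nothing deducted: "This yields around 98 babies per facility multiplied by 60 facilities for a total of 5,880 infants". The power list uses 20 versus 40 facilities for immunization and 20 versus 20 for each HIV contrast. Stated power ranges from 75% to 93%. The section closes by saying that "These power calculations represent lower bounds, as covariate analysis will further increase the actual power of the evaluation", and that all research questions have sufficient power.
- **Study Design and Procedures, Design.** The 17 frame facilities that are not drawn (77 − 60) form a fourth group, "4) Not in the study sample". They are not described as replacements.

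**The concern.** A reader of the Site Attrition paragraph would conclude that 60 already contains a margin, so that losing a few facilities would leave every contrast adequately powered. The power list does not bear this out. A calculation that includes an attrition allowance either computes power on the number expected to remain, or shows a smaller requirement and then inflates it. Neither appears here.

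This matters most for the two Simple versus Comparison contrasts stated at 75% and 76%. Both outcomes are in the protocol's list of primary outcomes, and both contrasts start below 80%, so any lost facility lowers power that is already short. A null result for the Simple Intervention on either outcome could then be read with more confidence than the design allows.

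**Working it through.** **Inputs, all from Sample Size and Justification.** k = 20 facilities per arm, n = 98 per facility, 5% significance level (sidedness not stated), and for each contrast a base rate, an absolute effect and a 95% plausibility interval.

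**Formula.** Power on the log-odds scale for a cluster-randomized binary outcome:

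- between-facility variance τ² = [(logit(upper) − logit(lower)) / (2 × 1.96)]²
- variance of the effect V = [τ² + 1/(n·p₁(1−p₁))]/k + [τ² + 1/(n·p₂(1−p₂))]/k
- non-centrality λ = (logit p₂ − logit p₁)² / V
- power from the non-central F distribution with 1 and 2k − 2 degrees of freedom, two-sided 5%.

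The protocol does not name its formula. This one was adopted because it reproduces the stated HIV figures.

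**Step 1: reproduce the two weak contrasts at k = 20.**

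*DBS PCR, Simple versus Comparison (5% to 9%, interval 1–10%).*
- τ² = [(−2.197 + 4.595)/3.92]² = 0.374
- Sampling terms: 1/(98 × 0.05 × 0.95) = 0.215 and 1/(98 × 0.09 × 0.91) = 0.125
- V = (0.374 + 0.215)/20 + (0.374 + 0.125)/20 = 0.0544
- Effect 0.631, λ = 0.631²/0.0544 = 7.32
- Power 75.0% (stated 75%)

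*HIV-positive mothers, Simple versus Comparison (0.2% to 1.0%, interval 0.1–1.0%).*
- τ² = 0.348
- Sampling terms 5.112 and 1.031
- V = (0.348 + 5.112)/20 + (0.348 + 1.031)/20 = 0.342
- Effect 1.618, λ = 1.618²/0.342 = 7.65
- Power 76.9% (stated 76%)

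One-sided tests would give 84.4% and 85.8%, which do not match, so the figures are two-sided.

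**Step 2: all six HIV contrasts, then with facilities removed.** With equal arms λ is proportional to k, so losing two per arm multiplies it by 18/20. For DBS PCR, Simple versus Comparison, 7.32 × 0.9 = 6.58 with 34 degrees of freedom, which gives 70.3%. The losses are assumed; the protocol gives no rate.

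| Contrast | Stated | 20 per arm | 18 per arm | 16 per arm |
|---|---|---|---|---|
| DBS PCR, Simple v Comparison | 75% | 75.0% | 70.3% | 64.9% |
| HIV-positive mothers, Simple v Comparison | 76% | 76.9% | 72.2% | 66.8% |
| DBS PCR, Comprehensive v Simple | 82% | 83.0% | 78.7% | 73.5% |
| Antibody, Simple v Comparison | 87% | 88.1% | 84.3% | 79.6% |
| HIV-positive mothers, Comprehensive v Simple | 87% | 87.5% | 83.7% | 78.9% |
| Antibody, Comprehensive v Simple (15% to 35%) | 93% | 93.6% | 90.8% | 87.1% |

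All six agree with the protocol to about one point at the full 20 per arm, so the stated HIV figures contain no hidden reserve.

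**Step 3: what 80% would need.** Scaling from the stated 75% and 76%, 80% power needs about 23 and 22 analysed facilities per arm, before any attrition allowance.

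**Step 4: immunization.** The same formula gives 91.4% for 40 versus 20, against 86% stated, so that figure is not reproduced. The two results agree only in that both exceed 80%.

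**The case against.** The strongest reply is that the trial was sized on immunization and that a margin exists there. By normal approximation, moving from 86% to 80% power takes 60 × 7.85/9.24 ≈ 51 facilities, which leaves about nine spare. The recomputation agrees in direction: 84.2% remains after losing four Comprehensive and eight other facilities. On this reading the attrition sentence could be true for the sizing outcome. This stands in part: the margin is real but undocumented, and it does not extend to the two contrasts that start below 80%.

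A second reply is covariate adjustment, which is the stated basis for the lower-bound remark and is footnoted to the 75% figure. The remark is not wrong in itself. But covariates are not facilities, and the only variance-explained figure, 60% to 70%, concerns immunization. If covariates removed 20% of between-facility variance (assumed), DBS PCR Simple versus Comparison would reach 81.0% at 20 per arm and 76.6% at 18. For HIV-positive mothers, Simple versus Comparison, even 60% removal (assumed) gives only 79.4% and 74.9%, because sampling variation dominates.

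Three stronger readings are tempting, and the protocol does not support them.

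- **That the power figures are really upper bounds.** This ignores the planned covariate adjustment.
- **That choosing immunization as the sizing outcome, "as this is the indicator with the smallest effect size required to be policy-relevant", is an error.** This depends on scale. Ten points exceeds most of the HIV effects in absolute terms, but relative to its base immunization is the smallest: 10/87 = 11%, against 4/9 = 44% for the nearest HIV contrast. A footnote says that percentage change is the primary indicator for immunization.
- **That facilities unable to implement would be excluded, biasing the comparison.** The protocol never says so. Register visits cover all 60 facilities, staffing losses can occur in any arm, and bounds analysis is planned for attrition. Bounds address bias, however, and do not restore power.

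**Conclusion.** The attrition sentence is wrong as written: the sample size section contains no added facilities, rate or inflation step. The consequence is limited to particular contrasts. Immunization and the three HIV contrasts stated at 87% to 93% can absorb some loss. DBS PCR and HIV-positive mothers, both Simple versus Comparison, are at 75% and 76% with every facility retained and would be at about 70% and 72% with 18 per arm. DBS PCR Comprehensive versus Simple would cross below 80%, at about 79%.

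The contradiction itself rests on the text alone. The sizes rest on the assumed loss of two per arm, no covariate adjustment, and a formula inferred from its match to the six HIV figures. It would go too far to conclude that the trial as a whole has no margin or that its randomised comparison is compromised.

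**What to change.** 1. Delete the reserve sentence, or state the number of facilities required before attrition and the allowance actually made.
2. Report each power at 18 as well as 20 facilities per arm (36 versus 18 for immunization).
3. Qualify the lower-bound remark: it applies to covariate adjustment with no facility lost.
4. Replace the statement that all research questions are sufficiently powered with one saying that two Simple versus Comparison contrasts, DBS PCR testing and HIV-positive mothers identified, are below 80% before covariates.

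The cost is protocol wording and a slightly less favourable power table. No change to the number of facilities, the visits or the data collection is needed.

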The study analysis will account for the risk of spillovers affecting the results of immunization uptake outcome variable between program and comparison facilities. Only one-third of facilities in the evaluation will be Comprehensive Intervention facilities which serve as the program group for the immunization uptake variable whereas the remaining two-thirds of the facilities will serve as a comparison group for this variable. There is a risk that, if the communication for the EID/EPI integration intervention is not properly targeted, mothers in comparison catchment areas may also receive the message. To minimize this risk, all messages will be highly associated to specific facilities via ANC, SMAGs, in-facility delivery, and PNC touch points, which are all facility-specific channels. However, the potential for word of mouth spread of information and communication spillovers remains. Therefore, the research team will analyze the immunization rates in the comparison sites against historical immunization data for these sites for significant changes over time. Finally, exit interviews will be conducted with comparison and program facility officials to check for observed changes in immunization attendance or rumors they may have heard from community members during the evaluation.

An additional spillover risk exists whereby mothers that ordinarily attend Comprehensive Intervention health facilities switch to other health facilities as a result of the Comprehensive Intervention. The study may collect immunization data from a subset of patients from health facilities neighboring Comprehensive Intervention facilities to estimate the magnitude of such potential shifts. Study sampling that maximizes the distance between study facilities will reduce the likelihood that comparison facility immunization rates are artificially increased due to new patients. Comprehensive Intervention facilities may still experience artificially low immunization rates due to transferring patients. Because estimating the proportion of patients that switch facilities that would remain at their typical catchment facility if the Comprehensive Intervention were universally implemented at every health facility would be extremely difficult, it is most appropriate to consider low immunization rates due to transferring patients as an impact of the Comprehensive Intervention although this could overestimate the effect the Comprehensive Intervention would have in a scaled-up environment.

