We will seek approval from the ERES Converge Ethics Review Board in Lusaka, Zambia and the Boston University IRB. Study staff will comply with the relevant proposal submission policies of ERES Converge in order to gain full ethical approval to conduct the proposed study. After ethical clearance, the proposal will also be submitted to MoH for final permission to conduct the study.

*Risks to participants*

The proposed evaluation is likely to expose individuals to a minimal level of risk. This section will split risks considered into three sections: risks involving patient attendance, risks involving patient’s health facility experience, and risks involving the management of personal data.

Risks involving patient attendance to under-five health facilities are restricted to the Comprehensive Intervention evaluation group. This evaluation will be measuring whether fewer mothers will attend immunization services due to stigma issues surrounding HIV-testing or inconvenience caused by longer appointment times. This represents one of the primary outcomes measured in the study and thus will be monitored very closely. To minimize any potential adverse effects to uptake of routine immunizations, the Comprehensive Intervention will be discontinued if at any time after two months of data collection Comprehensive Intervention facilities are confirmed to have an immunization rate more than 20 percentage points lower than comparison and Simple Intervention Facilities.^[[34]](#footnote-12)^

For Comprehensive Intervention facilities, the patient experience for mothers will change as a result of the administration of the rapid HIV antibody test for mothers not already confirmed to be HIV-positive. This change in testing procedure will be communicated to mothers during the group counseling session so they are fully informed if they would like to opt-out from the HIV testing. Health facility staff will conduct standard counseling protocols if a mother does allow the rapid HIV antibody test to be conducted. The counseling protocol will be done in private, and contain information about the implications of the test and further options. In this way, mothers will be fully informed throughout of the HIV testing procedures and possibilities during the facility visit.

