This study may estimate spillover effects due to patients transferring from Comprehensive Intervention to comparison facilities but will not attempt to estimate the proportion of transferred patients that would have remained at their original facility if the Comprehensive Intervention were universally implemented in all facilities. As a result, impacts on immunization rates are likely to be overestimated, and impacts on HIV-related indicators likely to be underestimated. Both of these biases are in the conservative direction. This is deemed acceptable given the policy-focus of this evaluation and that any study conclusions should account for the worst possible policy scenario – which the approach to spillovers should enable.

Finally, due to logistical considerations, the study does not attempt to integrate EID services with outreach EPI services, where health staff members travel to communities to administer routine under-five immunizations. Likewise, this will shade the impacts on immunization rates and HIV-related indicators conservatively, which is ideal to draw policy implications from the study.

Dissemination of Findings

The outcomes and analysis, along with a final recommendation, will be compiled into a study report and policy brief for the MoH and MoCDMCH. If this intervention is scaled up across the country, CHAI and IDinsight will continue to work with the partners to monitor the project’s status. Any findings from this longer-term monitoring period will be added to the policy brief. Contingent on MoH and MoCDMCH approval, findings will be shared with the Zambian and global health community to learn how EID testing rates can be increased and how HIV services can be better integrated with immunization services.

Budget

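### The Limitations treat the spillover biases as conservative and worst-case, but reason only from patient transfers; message spillover, which the protocol says remains, could shrink the measured immunization decrease

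*Protocol*

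**What the plan says.** The section on technical study risks and potential biases describes two spillovers that affect immunization uptake.

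- **Message spillover.** If communication about the integrated service is poorly targeted, "mothers in comparison catchment areas may also receive the message". Messages are to be tied to facility-specific channels, but the protocol concedes that "the potential for word of mouth spread of information and communication spillovers remains". In response, "the research team will analyze the immunization rates in the comparison sites against historical immunization data for these sites for significant changes over time", and officials at the facilities will be interviewed about attendance and rumours.
- **Transfers.** Mothers may leave Comprehensive facilities for others. The protocol counts the resulting fall as an impact of the intervention and accepts that this may overstate the effect at scale.

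The Limitations section returns to the subject with transfers only: "This study may estimate spillover effects due to patients transferring from Comprehensive Intervention to comparison facilities". From the decision not to separate out transfers that universal roll-out would prevent, it concludes that "impacts on immunization rates are likely to be overestimated, and impacts on HIV-related indicators likely to be underestimated", and adds: "Both of these biases are in the conservative direction". It closes with the assurance that "any study conclusions should account for the worst possible policy scenario – which the approach to spillovers should enable".

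Ethical Issues (Risks to participants) gives the mechanism of harm being monitored: "fewer mothers will attend immunization services due to stigma issues surrounding HIV-testing", or because visits take longer.

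**The concern.** The reassurance is wider than the argument behind it. A direction of bias is worked out for one spillover and then used to vouch for the study's conclusions generally. The spillover left out can act the other way: deterrence in the comparison catchments lowers the reference rate and so reduces the measured decrease.

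This matters because the trial aims to raise HIV testing without reducing immunization, and the immunization null hypothesis is that there is no decrease. Bias toward zero therefore favours the reassuring conclusion. A policymaker who has read the Limitations would take a null or small decrease as safe with room to spare, when a real harm might have been diluted. The discontinuation comparison under Ethical Issues uses the same contrast and should be read with this in mind; no change to that rule is suggested here.

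**Working it through.** **Inputs from the protocol** (Sample Size and Justification, immunization outcome): 20 Comprehensive facilities against 40 Simple and Comparison facilities, 98 infants each, expected DPT1 uptake 87% (plausibility interval 55% to 95%), detectable decrease 10 points, significance level 5%, stated power 86%. **Assumed**, because the protocol gives no value: *s*, the share of the true harm that message spillover reproduces at comparators.

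**1. The plan's own figure.** On the logit scale, between-facility SD = [logit(0.95) − logit(0.55)]/(2 × 1.96) = 0.70, so variance = 0.490. Adding sampling variance 1/(98·p(1−p)) in each arm gives SE = √(0.580/40 + 0.548/20) = 0.205. The effect is logit(0.87) − logit(0.77) = 0.693, so the ratio is 3.38. Two-sided power is about 0.91 (0.90 to 0.92 across variants), not 86%. The protocol does not state sidedness. Step 3 therefore uses both baselines; the point about direction depends on neither.

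**2. Message spillover alone.** With true harm D, the measured decrease is

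(87% − sD) − (87% − D) = (1 − s)D.

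For D = 10 points: 9 at s = 0.10, 8 at s = 0.20, 7 at s = 0.30.

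**3. Effect on power, illustrative.** Taking the stated 86% as two-sided, SE = 10/(1.960 + 1.080) = 3.29 points and power = Φ(d/3.29 − 1.96).

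| s | measured decrease d | power from stated 86% | power, logit model of step 1 |
|---|---|---|---|
| 0 | 10 | 86% | 91% |
| 0.10 | 9 | 78% | 83% |
| 0.20 | 8 | 68% | not run |
| 0.25 | 7.5 | not run | 65% |
| 0.30 | 7 | 57% | not run |

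**4. Both spillovers together.** Suppose uptake at Comprehensive facilities falls by 10 points, a share *t* of which is transfers, and all transfers are absorbed by the 40 comparators (equal facility sizes assumed). The true loss of immunization is 10(1 − t), and the measured decrease is

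10 + 10t × 20/40 − s × 10(1 − t).

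| t | true loss | s = 0 | s = 0.10 | s = 0.25 | s = 0.50 |
|---|---|---|---|---|---|
| 0.10 | 9.0 | 10.5 | 9.6 | 8.25 | 6.0 |
| 0.50 | 5.0 | 12.5 | 12.0 | 11.25 | 10.0 |

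The measured decrease falls below the true loss when 10 + 5t − 10s(1 − t) < 10(1 − t), that is, when s > 1.5t/(1 − t). At t = 0.10 the threshold is s = 0.15/0.90 = 0.17. At t = 0.50 it is 1.5, which cannot be reached while s is at most 1. The sign of the net bias therefore depends on two quantities that the protocol does not fix.

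**The case against.** **The closing sentence may mean only the handling of transfers.** The paragraph opens with transfers, and its wording is hedged. That reading is available, but it does not save the assurance. The sentence speaks of any study conclusions, and treating transfers as impact cannot deliver a worst case while another acknowledged spillover may pull the other way.

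**Message spillover is disclosed and watched.** This stands. A reader might infer that the protocol ignores it; it does not. It limits the channels, checks comparison sites against their own history and interviews officials. But these steps detect a fall at comparison sites, and the historical check is also open to secular trend. None corrects the contrast or supports calling it conservative.

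**The direction is inferred.** This also stands. A reader might infer that message spillover would lower comparison uptake and that the trial will understate harm. The protocol says neither. Only the stigma route clearly carries over. Harm from longer visits would spread little, because comparison sites do not change their procedures, and an encouraging message would raise uptake. The supportable word is could.

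**The sizes are assumed.** The spillover shares have no source in the protocol. The 86% baseline was not reproduced, and the protocol expects covariates to add power. A reader might take the lower powers in the table as properties of this trial; they are illustrations only.

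**Conclusion.** The worst-case assurance is wrong as written. It rests on one of two spillovers that the protocol itself names, and under the protocol's stigma mechanism the other could bias the measured immunization decrease toward zero. The net direction is unknown, so a null or small decrease cannot be presented as an upper bound on harm.

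The size cannot be fixed from the document. Under the assumed range of 10% to 30% reproduction at comparators, with no transfers, a true 10-point harm appears as 9 to 7 points. With transfers included, the net error can have either sign. The conclusion does not rest on the stated power, and it does not establish that harm will be understated.

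**What to change.** In the Limitations, confine the conservative claim to patient transfers, state that message spillover could shrink the measured immunization decrease and that the net direction of bias is not known, and delete the worst-case assurance. The cost is a few sentences; design, sample and primary analysis are unchanged.

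Optionally, where facility locations are available, report a sensitivity analysis with confidence limits: Comprehensive facilities against only those comparators whose nearest study neighbour is not Comprehensive. If geography is unrelated to arm, and ignoring stratification, 20/59 = 34% of comparators (13.6 of 40) would drop out, leaving about 26. The standard error grows by √[(1/20 + 1/26.4)/(1/20 + 1/40)] = 1.08, about 8%. Working from the stated 86%, power for 10 points would be about 80%.

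The report should state the limits of this analysis. Comparators near a Comprehensive facility are also the likeliest to receive transferring mothers, so excluding them removes both effects together and cannot separate them. The nearest alternative may also be one of the 17 frame facilities outside the sample (77 − 60). For these reasons it should not become a second condition for concluding no harm.
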